#### Strategies to improve adherence to interventions {11c}

Prior to the inclusion of a participant, an explanation about EMDR therapy is given in the Patient Information Form and, if desired, questions are answered during the telephone call in which exclusion criteria are checked. Again, later, during the intake subjects are informed thoroughly about what to expect during and after an EMDR treatment session. This increases motivation and adherence to the therapy once treatment has started.

Beforehand, trial therapists are required to demonstrate their competence in applying the treatment. As yet, there are three trial therapists, but more may be added later. To ensure treatment quality and adherence to the EMDR standard protocol, the therapists receive monthly supervision sessions by the EMDR consultants based on the EMDR treatment sessions videotaped during the study. Furthermore, weekly session checklists are viewed by the consultants to closely follow the EMDR process. Any questions by the therapists will be answered before the next session. Also, every session is videotaped to enable regular fidelity checks. Fifteen percent of all recorded sessions will be reviewed for treatment fidelity using the Treatment Integrity Checklist for EMDR. Fidelity checks will be done at random, by the last author ([name]), who is an EMDR Europe registered EMDR consultant with extended expertise.

#### Relevant concomitant care permitted or prohibited during the trial {11d}

Concurrent treatment for psychotrauma is an exclusion criterion. Upon entering the study, participants agree to refrain from starting other treatments (medication, nutritional supplements) or behavioral changes (e.g., diet) aimed at the IBS symptoms.

Treatments and diets that are already part of the patients’ customary regimen can be continued. We ask subjects to report any changes in their prescribed medication. At three measurement moments, subjects are explicitly asked about their current medication use.

#### Provisions for post-trial care {30}

Subjects from both the intervention and wait-list control group will after the end of the study meet with the principal investigator to determine if there is (still) a wish or need for treatment for the IBS symptoms. If so, they are offered treatment appropriate to their current situation, provided that this can be offered by the Department of Clinical Psychology of the Diakonessenhuis. In some cases, referral to mental healthcare may be the best course of action.

No harm is expected to occur from participating in the study and the medical ethical committee has agreed to grant an exemption for an insurance for the participants of the study. The hospital, however, has, as required by law, a liability insurance for compensation of those who suffer from harm incurred in the hospital.

### Outcomes {12}

The primary outcome of this study is the intensity of abdominal pain. As the intensity of abdominal pain in IBS can vary greatly from day to day, we have chosen to pose the same question each day for 2 weeks. Participants answer the question: “How much did you suffer from abdominal pain during the last 24 h?”. The subject’s answer is given on a 21-point Likert scale (0 = no pain, 10 = worst pain imaginable, half points possible).

In addition to the primary outcome measure (abdominal pain), we pose four other diary questions at the same time, during the same period, with the same 21-point Likert scale. Based on their statements at inclusion about their principal IBS symptoms, we ask about their top two symptoms (abdominal pain excluded): “How much did you suffer from (complaint) during the last 24 h?” (0 = not at all, 10 = extreme suffering, half points are possible). These symptoms could be frequently occurring IBS symptoms such as diarrhea, constipation, and bloating, but they can also be more idiosyncratic such as dizziness. We also ask about the hindrance subjects have experienced from their IBS symptoms when engaging in everyday activities. Based on their statements at inclusion about the two- valued activities that are most impeded by the IBS symptoms, we ask for every one of these activities: “How much hindrance have you experienced from your IBS symptoms when engaging in this activity?” (0 = no hindrance at all, 10 = made completely impossible; half points possible). Activities most likely to be impeded by IBS symptoms are working, doing sports, going out for dinner, and going out (dancing, theatre, etc.).

The 14-day-sequence of these 5 “diary questions” is administered at inclusion, 8 weeks after inclusion (for the intervention condition this means after treatment), and at follow-up (20 weeks after inclusion, 3 months after treatment).

In addition to the diary questions, we administer several questionnaires, the purpose of which is to describe the population and to either confirm or disconfirm the results of the diary questions. They also enable comparing outcomes with those of other studies. The questionnaires are administered on the last day of every 14-day-sequence of diary questions.

The questionnaires administered are:IBS-SSS (Irritable Bowel Syndrome—Severity Scoring System) [35].

The first part of this questionnaire consists of 5 questions regarding the frequency and intensity of pain, the intensity of bloating, satisfaction with bowel movements, and the impact of IBS on the subject’s life in general. The answer type varies per question (Visual Analog Scale 1–100 or a specific number). Scores can range from 0 to 500 with higher scores indicating more severe symptoms (75–175 mild, 175–300 moderate, > 300 severe). The IBS-SSS severity score is recognized by the Rome Foundation as an appropriate measure for assessing changes in research on treatments [36]. A decrease of 50 points is considered a clinically relevant improvement.

Part two of the IBS-SSS consists of 5 questions that explore the nature and quality of the symptoms. In this study, only the localization of abdominal pain is addressed.2)IBS-QOL (Irritable Bowel Syndrome—Quality of Life measurement) [37]

This questionnaire measures the impact of IBS on quality of life. It contains 34 statements covering the following 8 areas: Dysphoria, Interference with Activity, Body Image, Health Worry, Food Avoidance, Social Reaction, Sexual, and Relationships. Subjects are asked to indicate to what extent each of these statements applies to them on a 5-point Likert scale (1 = not at all, 5 = very much). The individual responses to the 34 items are summed and averaged for a total score and then transformed to a 0–100 scale for ease of interpretation with higher scores indicating better IBS-specific quality of life. In addition to the total score, a scale score can be calculated for each of the 8 areas mentioned. Distribution of the IBS-QOL is managed by the Rome Foundation. Psychometric properties are well established [38].3)AR (Adequate Relief Question)

This is one question: “In the last 7 days, have you had adequate relief of your IBS symptoms?” The answer can be yes or no. The Rome Foundation accepts and recommends this outcome measure in RCTs [39, 40]. In this study, AR is included as an outcome measure to allow comparison of our results to those of studies using this recommended outcome measure.

Other questionnaires, not used as outcome measures, but solely administered to describe the population are:LEC-5 (Life Events Checklist for the DSM-5) [41]

This questionnaire is a self-report measure designed to screen for potentially traumatic events in a respondent's lifetime. It describes 17 (A criterion) events, and subjects are asked to indicate whether they have experienced such an event and in what way (happened to me, witnessed it, learned about it, part of my job, not sure, doesn’t apply). There is no formal scoring protocol or interpretation per se, other than identifying whether a person has experienced one or more of the events listed. The LEC-5 in combination with the PCL-5 can be used to screen for PTSD.

In this study, the LEC-5 in combination with the PCL-5 is used to screen for PTSD criteria.b)PCL-5 (PTSD Checklist for the DSM-5)

This self-report questionnaire consists of 20 items concerning the 20 DSM-5 symptoms of PTSD. For each symptom, subjects are asked to indicate on a Likert scale to what extent they have suffered from it in the past month (0 = not at all, 1 = a little bit, 2 = moderately, 3 = quite a bit, 4 = extremely). A total symptom severity score (range 0–80) can be obtained by adding the scores of the 20 items together. DSM-5 severity scores for the individual symptom clusters can be obtained by summing the scores of the items of a particular cluster. The PCL-5 can be used in combination with the LEC-5 (see below) as a screening tool for PTSD. An indication for a PTSD diagnosis can be obtained by counting any item with a score of 2 (moderate) or higher as a symptom that is present. Then the DSM-5 diagnostic calculation rule is followed to ascertain whether the required criteria are met: a minimum of 1 B-symptom (questions 1–5), 1 C-symptom (questions 6–7), 2 D-symptoms (questions 8–14), and 2 E-symptoms (questions 15–20). The PCL-5 can also be used to determine the course of PTSD symptoms. Results from the USA with the previous version of the PCL (PCL for DSM-IV) suggest that a 5–10-point change indicates a reliable change and a 10–20-point change indicates a clinically significant change [42].

In this study, the PCL-5 is used to assess the severity of PTSD symptoms.

Diary questions and questionnaires are administered digitally, using an ISO 9001-certified online tool. Subjects receive an e-mail containing a link to the diary questions or the questionnaire, which they then can fill out.

### Participant timeline {13}

The recommended schematic diagram is showed in Additional file 1.

*The intake session takes place the day after the questionnaires, and the other sessions take place on the same day, each a week later. See Fig. 2 for the overview.

**Fig. 2 Fig2:**
[figure not shown]
Participant timeline overview for both EMDR treatment group and wait-list control

**The questionnaires are administered on the last day of the 2-week diary period.

### Sample size {14}

Several factors have influenced the sample size in this study: setting, method of analysis, and the estimate of comparability with previous scientific research.

As the study is conducted as part of the curriculum of a training course taken by the principal investigator, both time and resources are limited. Our aim is to demonstrate a clinically relevant treatment effect regarding the primary outcome measure with a limited sample size.

The design of our study enables us to analyze our primary outcome data (pain score diary) using a linear mixed effects models analysis. Sample size was computed using the online statistical calculation program GLIMMPSE (General Linear Mixed Model Power and Sample Size): https://glimmpse.samplesizeshop.org/#/ using an alpha of 0.05 and a desired minimum power of 0.80.

The most important estimated value required by the GLIMMPSE program is the expected effect size. Since a study on the effect of EMDR on abdominal pain in IBS has never been done before, a search was made for comparable research. A review on EMDR treatment for chronic pain found large effect sizes [22]. The EMDR for phantom limb pain study design is most comparable to our study design [28]. Based on this study, a remarkably large effect size d of 1.22 was calculated. On entering this effect size, GLIMMPSE calculated that a sample size of 12 should be sufficient. However, when a demonstration of an average effect size is wanted, a sample size of 24 is needed. This sample size is adequate to analyze the primary outcome measure daily pain scores using a linear mixed effects model. In addition, this sample size is also expected to be adequate to analyze the secondary outcome measures from the standardized questionnaires (measures taken only three times in total) with LME models. Taking drop-out into account we decided to include a maximum of 34 participants.

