The outcome measures from the two standardized questionnaires, which only yield 3 data points, will be analyzed by LME models based on 2 groups (treatment and control) and 3 measuring moments (at baseline, after treatment, and at follow-up). See Fig. 2.

For all analyses regarding symptom improvement, a one-sided significance threshold of alpha = 0.05 will be used. For all other analyses, a two-sided* p* value of 0.05 will be used as the significance threshold. We will report both *p*-values and 95% confidence intervals.

Based on the Adequate Relief Question, and based on the presence of a clinically relevant reduction of symptoms as measured by the IBS-SSS, a Number Needed to treat will be calculated, for two measuring moments: after treatment and at follow-up.

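### The adopted sample size of 24 is tied to an effect with no number; scaled from the plan's own figure of 12 at d = 1.22, it gives 80% power only for d of about 0.7–0.8

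*Protocol article*

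**What the plan says.** All of this is in the protocol article, Sample size {14}, unless stated otherwise.

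- The calculation was run in GLIMMPSE "using an alpha of 0.05 and a desired minimum power of 0.80". The section does not say whether alpha is one- or two-sided. Statistical methods {20a} says that for symptom improvement "a one-sided significance threshold of alpha = 0.05 will be used".
- From a comparable phantom limb pain study, "a remarkably large effect size d of 1.22 was calculated". The text continues: "On entering this effect size, GLIMMPSE calculated that a sample size of 12 should be sufficient".
- The figure the trial adopts follows: "when a demonstration of an average effect size is wanted, a sample size of 24 is needed". No d is attached to it.
- For the standardised questionnaires, taken three times, the section adds that "this sample size is also expected to be adequate to analyze the secondary outcome measures". No calculation is given.
- Enrolment is capped at 34 to allow for drop-out. Concealment mechanism {16b} has 34 envelopes, so 24 must be a total over both arms.

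**The concern.** With the design and variance inputs fixed, the detectable effect falls roughly with the square root of the sample size. Doubling from 12 to 24 therefore cannot bring it down from 1.22 to a medium effect. A reader who sees *average* next to a review with large effects and a d described as remarkably large will probably take it as medium. On that reading the section promises 80% power that its own first figure does not support. A null result could then be read as excluding a medium effect with good power, when the trial was not sized for that.

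**Working it through.** **Inputs from the protocol article.** Alpha 0.05, power 0.80, d = 1.22 with N = 12, N = 24 for the unnumbered effect, maximum 34 (all {14}); 1:1 allocation ({16a}); one-sided 0.05 for symptom improvement ({20a}); a period-by-condition interaction over three periods, which has 2 df ({20a}). The section gives no SD, correlation or contrast.

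**1. Reproducing the plan's figure of 12.** A plain two-group t-test at d = 1.22, with no gain from repeated measures, needs 24 in total two-sided or 20 one-sided. As a total, 12 is reached only if the repeated measures multiply the effective d by some factor k. The figure of 24 cannot be reproduced, because its effect size is not given.

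**2. Calibrating k.** Let D(N) be the standardised effect that gives 80% power at total N. It comes from the noncentral t distribution with N − 2 df and noncentrality D√(N/4), or from the noncentral F with 2 and N − 3 df and noncentrality D²N/4.

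| Test | D(10) | D(12) | D(24) | D(34) |
|---|---|---|---|---|
| t, two-sided | 2.02 | 1.80 | 1.20 | 0.99 |
| t, one-sided | 1.72 | 1.54 | 1.05 | 0.87 |
| F, 2 df | 2.47 | 2.14 | 1.36 | 1.12 |

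If 12 is the smallest sufficient even total (12 reaches 80%, 10 does not), k lies between D(12)/1.22 and D(10)/1.22. This gives 1.47–1.66 two-sided, 1.27–1.41 one-sided and 1.75–2.03 for the 2-df test.

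**3. Carrying k to 24 and 34.** Detectable d = D(N)/k. For example, two-sided at 24: 1.20/1.47 = 0.81 and 1.20/1.66 = 0.72.

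| Test | Detectable d, N = 24 | Detectable d, N = 34 | Power for d = 0.5, N = 24 | Power for d = 0.5, N = 34 | N for d = 0.5 |
|---|---|---|---|---|---|
| t, two-sided | 0.72–0.81 | 0.60–0.67 | 0.41–0.49 | 0.55–0.65 | 48–60 |
| t, one-sided | 0.74–0.83 | 0.62–0.69 | 0.44–0.51 | 0.56–0.65 | 52–64 |
| F, 2 df | 0.67–0.78 | 0.55–0.64 | 0.41–0.53 | 0.58–0.71 | 42–54 |

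Plain square-root scaling gives 1.22/√2 = 0.86 at 24.

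**4. Reverse check.** If 24 in total gave 80% power for d = 0.5, k would have to be D(24)/0.5 = 2.39 two-sided (2.10 one-sided, 2.73 for the 2-df test). With that k, 12 patients would have over 99% power at d = 1.22, and the smallest sufficient total would be 6 to 8, not 12.

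**5. Per-arm readings.** If 12 is per arm, it matches the plain two-sided t-test (24 in total), but then 24 in total detects only d = 1.20. If 24 were per arm, 48 patients would be needed, which exceeds the maximum of 34.

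**6. Questionnaires.** The plan gives no correlation. Assuming r = 0.5–0.7, power for d = 0.5 at 24 is 0.22–0.33 for a two-sided change score, where k = 1/√(2(1 − r)). It is 0.39–0.51 for a one-sided baseline-adjusted comparison, where k = 1/√(1 − r²). The second range overlaps the diary range of 0.41–0.53.

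**The case against.** Two sample sizes and one d cannot conflict until someone supplies the second d. The section never says that *average* means 0.5. It could mean typical for this literature, and at d of about 0.75–0.8 the figures 12 and 24 agree. The scaling also assumes that 12 is a total, that it is the smallest sufficient number, and that both runs used the same contrast and correlations. The article confirms none of these, and a condensed article may leave power inputs to the full protocol.

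Most of this stands, and it limits the conclusion. A reader might infer that the two figures flatly contradict each other, or that the trial has only even odds of detecting an average effect. The article does not support either statement. The first depends on reading *average* as medium. The second also ignores that up to 34 may be analysed, where power for d = 0.5 is 0.55–0.71. A reader might also infer that adequacy for the questionnaires is impossible. The overlapping ranges in the working do not show that.

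The objection does not remove the gap. Brevity does not explain it, because the section prints the d for the number it did not adopt and omits it for the number it did. The per-arm readings do not rescue the figure either.

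**Conclusion.** The point holds in conditional form. The section ties 80% power at 24 to an effect it does not quantify. On the plan's own calibration, that power applies to d of about 0.7–0.8 (0.67–0.83 across tests), which is near-large, and at 34 to about 0.55–0.7. This rests on 12 being the smallest sufficient total and on shared inputs in both runs.

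Only under the further assumption that *average* means d of about 0.5 do the figures disagree. Power is then 0.41–0.53 at 24 and 0.55–0.71 at 34, and about 42–64 patients would be needed. The questionnaire statement is unsupported, not shown to be false. The section should be corrected, because the stated size and power will frame how a null result is read.

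**What to change.** Rewrite section {14} from the stored GLIMMPSE runs:

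- Give the numeric d used for 24, and say whether 12 and 24 are totals or per arm.
- State the sidedness of alpha, the contrast tested and the correlations entered.
- Unless the original run shows otherwise, replace the wording about an average effect with the detectable d recomputed from those inputs at 24 and at 34. On the calibration here these are about 0.7–0.8 and 0.55–0.7. They are back-calculated and should not be printed in place of the actual run.
- State the power for d = 0.5 at both sizes.
- Back the questionnaire statement with a computed power, or remove it.

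The cost is a rewording and possibly a less favourable stated power. No extra patients are needed, and the analysis does not change.

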### Recruitment {15}

An agreement has been made with all gastroenterologists and physician assistants in gastroenterology at Diakonessenhuis that—at the end of their consultation—they will issue the initial screening questionnaire to all their outpatients who meet the Rome IV criteria for IBS. This initial screening instrument, which encompasses the first 5 questions of the IBS-SSS, is also used as a routine outcome measurement in gastroenterology for more general purposes. The time invested by the gastroenterologist at the outpatient GI clinic is kept at a minimum, and regular reminders to hand out the screeners are sent to all gastroenterologists.

An initial estimate was made by the liaison gastroenterologist of how many patients are expected to meet the initial criteria. This estimate turned out to be too optimistic; in the first 6 months, about 30 screening questionnaires were filled out. Roughly 25% of these patients (*N* = 7) met the initial inclusion criteria.

## Assignment of interventions: allocation

### Sequence generation {16a}

The allocation sequence is generated in advance by using the Excel randomization function. Allocation of treatment vs wait list (control) is 1:1.

### Concealment mechanism {16b}

The outcome of the randomization is placed in 34 opaque, sealed envelopes, and the rank number of inclusion is written on the envelope. This is done by an independent person, not involved in the study. The sealed envelopes are kept in a locked cabinet. After receiving informed consent, the participant is assigned an ID number, after which the corresponding envelope is opened. Once allocated to either treatment or wait-list condition, blinding is no longer possible.

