## Trial design {8}

The present study is a superiority study comparing the EMDR intervention with a wait-list control group in a two-armed randomized controlled trial. Patients will be randomly allocated to either EMDR treatment or wait list, with an equal allocation ratio. Blinding for the intervention is not possible.

This study is registered at The Netherlands Trial Register, with registration number NL8894. It is thereby automatically included in the International Clinical Trial Registry Platform.

For an overview of the study design, including recruitment, random allocation, assessments, and treatment, see Fig. 1.

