#### Criteria for discontinuing or modifying allocated interventions {11b}

With acquiring new information during sessions, the case conceptualization can change a little, which in turn can change the selection of memories to be processed. The EMDR treatment in itself will not be altered.

Patients are free to withdraw from partaking in the study at any time. The research team can decide to remove a patient from the study if.There are serious medical reasons.The subject fails to complete the questionnaire(s) during the first period of measurements.The subject fails to appear at a treatment session more than twice (without notice).The subject’s non-cooperation seriously hinders treatment.Subject meets an exclusion criterion along the way (e.g., becomes pregnant or an intestinal disease is diagnosed).There are persistent serious side effects.

Like all studies involving human subjects, we are required to report serious adverse events as defined by the Central Committee on Research Involving Human Subjects (in Dutch: CCMO, Centrale Commissie Mensgebonden Onderzoek).

No serious adverse effects have been found in studies of EMDR in diverse populations. Some discomfort—both physical and psychological—both during sessions and in the first 4 days after an EMDR session is not unusual. As this is part of the psychological process of processing negative memories, this is no cause for discontinuing the intervention.

Any unexpected adverse effects will be discussed within the research team, which includes two EMDR Europe registered EMDR consultants with extended expertise. Depending on the outcome of this deliberation, steps will be taken to reduce the adverse effects. If necessary, participation in the study will be temporarily interrupted. If the adverse effects persist, participation in the study will be discontinued.

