### Implementation {16c}

An independent person generates the allocation sequence and prepares and keeps the sealed envelopes. The main investigator will obtain the next sealed envelope from this person after informed consent was given. The note of allocation (treatment or control) and the numbered envelope are attached to the informed consent form. The main investigator then informs the participant about allocation. Allocation to a specific therapist depends mostly on the therapists’ schedules and timing of enrollment.

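### Nothing in the plan holds back allocation until the 14-day baseline diary is complete, so the self-rated pain baseline may be reported by patients who know their arm

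*Protocol article*

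**What the plan says.** Concealment mechanism {16b} gives the sequence as consent, ID number, envelope: "After receiving informed consent, the participant is assigned an ID number, after which the corresponding envelope is opened". It adds that "the rank number of inclusion is written on the envelope". Implementation {16c} repeats the trigger, "The main investigator will obtain the next sealed envelope from this person after informed consent was given", and continues: "The main investigator then informs the participant about allocation". Neither section mentions the baseline diary.

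Outcomes {12} says that the 14-day diary "is administered at inclusion, 8 weeks after inclusion (for the intervention condition this means after treatment"), and again at 20 weeks. It also says: "The questionnaires are administered on the last day of every 14-day-sequence of diary questions". Participant timeline {13} puts the intake session on the day after those questionnaires.

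Trial design {8} describes the overview figure as "including recruitment, random allocation, assessments, and treatment, see Fig. 1". Criteria for discontinuing or modifying allocated interventions {11b} lets the team remove a participant when "The subject fails to complete the questionnaire(s) during the first period of measurements".

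Statistical methods {20a} specifies intention-to-treat and answers the primary question by the interaction of measurement period with condition, with baseline as the period against which the other two are compared. Who will be blinded {17a} says that participants cannot be blinded.

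**The concern.** If these steps are followed as written, a patient signs consent, learns whether treatment or waiting comes next, and then rates pain daily for 14 days. Those ratings are the reference for the primary contrast. Anticipation, relief or disappointment could move them differently in the two arms before any EMDR is given, and the analysis could not separate such a movement from a treatment effect.

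Unblinded ratings after treatment are unavoidable in this design. An unblinded baseline is avoidable.

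There is a second consequence. If allocation comes first, removing someone for an incomplete first measurement period is a post-randomisation exclusion that may depend on the arm. That is in tension with the intention-to-treat statement. It would also use up one of the 34 envelopes, which equal the maximum sample.

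**Working it through.** The plan states no figure on this point that could be reproduced. The check has two parts: the order of events, and the size of the consequence.

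**Order of events**

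- {16b} and {16c}: consent is the only stated trigger for opening the envelope, and disclosure to the patient follows. Completing the diary is not a condition.
- {8}: random allocation is listed before assessments. This describes what a figure contains, so it is supporting evidence only.
- {11b}: failure to complete the first measurement period appears among the rules for allocated interventions. The heading is a SPIRIT checklist item, so this too is only supporting evidence.
- {12} and {13}: counting the first diary day as day 1, the diary fills days 1–14, the intake falls on day 15, and the seven weekly sessions fall on days 15, 22, 29, 36, 43, 50 and 57. Eight weeks after day 1 is day 1 + 56 = 57, so the post-treatment point fits if inclusion is the start of the diary.
- That count does not settle the order. If inclusion meant the end of baseline, the seventh session would fall at about week 6, a diary over weeks 6–8 would put the questionnaires at week 8, and week 20 would be 12 weeks later. This fits about as well.
- No section places the diary before allocation, and none says outright that the envelope is opened before diary day 1.

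**Effect on the contrast**

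Let b₀ be the difference (EMDR minus wait list) in the reporting shift at baseline caused by knowing the arm, and b₁ the same difference at the later period. With improvement defined as baseline minus later pain:

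bias in the between-arm difference in improvement = b₀ − b₁.

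If the shift is confined to baseline (b₁ = 0), the bias is b₀. If it persists unchanged (b₁ = b₀), the bias is 0. A positive b₀ (higher baseline reports under EMDR) exaggerates the benefit, and a negative one shrinks it.

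**Size, on assumed values**

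From the protocol: 24 patients ({14}) allocated 1:1 ({16a}), so 12 per arm; one-sided alpha 0.05 ({20a}). Assumed: b of ±0.2 or +0.3 SD confined to baseline, a correlation ρ between period means of 0.5 to 0.8, and a single baseline-to-later contrast with a normal approximation.

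SE = √(2(1 − ρ)) × √(2/n); rejection probability with no true effect = Φ(b/SE − 1.645).

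Example with n = 12, ρ = 0.5, b = +0.2: SE = 1 × 0.408 = 0.408; 0.2/0.408 = 0.490; Φ(0.490 − 1.645) = Φ(−1.155) = 0.124.

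| n per arm | ρ | b = −0.2 | b = 0 | b = +0.2 | b = +0.3 |
|---|---|---|---|---|---|
| 12 | 0.5 | 1.6% | 5% | 12.4% | 18.1% |
| 12 | 0.7 | 1.1% | 5% | 15.6% | 24.3% |
| 12 | 0.8 | 0.8% | 5% | 19.2% | 31.5% |
| 17 | 0.5 | 1.3% | 5% | 14.4% | 22.1% |
| 17 | 0.7 | 0.8% | 5% | 18.6% | 30.3% |
| 17 | 0.8 | 0.5% | 5% | 23.5% | 39.7% |

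The rows with 17 per arm use the maximum of 34.

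The opposite direction costs power. With an assumed true effect of 0.5 SD, 12 per arm and ρ from 0.5 to 0.8, power falls from 34–62% at b = 0 to 18–32% at b = −0.2.

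**The case against.** **The order is inferred.** The allocation sections say only that disclosure follows consent, and inclusion can be read as the end of baseline. Figs. 1 and 2 and Additional file 1, which would show the schedule, are not available here. A reader might infer that the protocol states that patients are told before diary day 1; it does not. This limit stands. What remains is that the text as written permits that order, several sections point to it, and none rules it out.

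**The bias is conditional.** A reader might infer that any shift caused by knowing the arm carries over in full, or that it must favour EMDR. Neither follows. A persistent shift cancels, and relief in the EMDR arm or disappointment on the wait list would work against the superiority hypothesis.

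**The size is assumed.** The protocol gives no SD, correlation or shift. Nor can a shift be set against a detectable effect taken from the plan: Sample size {14} names an average effect size without a value. A single comparison with 12 per arm, one-sided 0.05 and 80% power detects (1.645 + 0.842) × √(2/12) ≈ 1.02 SD, and a smaller figure needs a correlation that the plan does not disclose.

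**Removal is discretionary.** {11b} says that the team may remove such participants, and {20c} has the mixed model use all available data. Exclusion from the analysis is therefore possible, not automatic.

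**The larger unblinding problem remains, and timing is late.** Self-report at weeks 8 and 20 is unblinded whenever the envelope is opened. The Discussion acknowledges the lack of blinding and the placebo response, though not that baseline may be affected. Trial status gives 31 December 2023 as the estimated end of recruitment, and the article appeared on 4 December 2023, so reordering the steps can reach few participants, if any.

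**Conclusion.** The point holds in a limited form. The plan makes consent, not a completed baseline, the condition for opening the envelope and telling the patient, so the reference period of the primary interaction may consist of unblinded self-ratings. That allocation precedes the diary is the best-supported reading, but it is unconfirmed.

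The harm depends on a differential shift that is present at baseline and fades later; its direction is unknown. On the assumptions shown, with 12 per arm, +0.2 SD takes the false-positive rate from 5% to about 12–19%, and −0.2 SD takes it to about 1–2% with a loss of power. These figures show how sensitive a trial of this size is. They do not estimate a bias that has occurred.

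Use of the {11b} removal criterion for incomplete baseline would, under the same order of events, be a post-randomisation exclusion in tension with intention-to-treat.

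**What to change.** 1. State in {16b} and {16c} when allocation is disclosed relative to the diary. For any participant still to be enrolled, open the envelope and disclose allocation only after the baseline diary and questionnaires are complete. Those who do not complete baseline then leave before randomisation. N, alpha and the visits do not change. The costs are amendment wording and an intake slot that must be held or booked at short notice.
2. For participants allocated before baseline, keep all of them in the intention-to-treat analysis whether or not baseline was completed.
3. Pre-specify a sensitivity analysis that compares post-treatment and follow-up pain between arms with the screening IBS-SSS pain score as covariate in place of the diary baseline. That score is collected before consent ({26a}), so allocation cannot have affected it. Note its weakness: it is a single item truncated at 60 or more by eligibility ({10}), so it will explain less variance than the diary would. The cost is one additional model.
4. If allocation did come first, report the unblinded baseline as a limitation beside those already in the Discussion. With recruitment near its planned end, items 2 to 4 are the practical remedy for most participants.
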